## Methods

### Setting

WACHS delivers healthcare services to over 550,000 people across 2.5 million square kilometres.^24,25^ There are 103 WACHS-run health facilities, including six large regional hospitals, 15 medium-sized district hospitals, 48 small hospitals, and 34 health centres and nursing posts across seven geographically dispersed regions. There are additional non-WACHS health facilities and Aboriginal Medical Services that are outside the scope of this research.

The majority of smaller health facilities are operated by generalist nurses, with medical cover provided by a local general practitioner. Each region is unique in its population, geography, health needs, and service availability, and all classified as rural and remote according to the Australian Statistical Geography Standard (ASGS) Remoteness Structure.^
1
^ The ASGS is based on the road distances people have to travel for services.^
1
^
Figure 1 shows the seven WACHS regions, overlayed with the measure of remoteness.

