RE-AIM dimension	Expanded RE-AIM & IOF definition	Data measure	Data collection
Reach	Number of individuals exposed to the intervention	Number of CC patient contacts (by site, health facility type, region) for each command centre service	Service data
	Proportion of intended audience who participate in the intervention	Proportion of CC patient contacts compared to total health facility presentations	Service data
	Representativeness of individuals relative to the intended population	CC Patient contact characteristics (age group, sex, postcode, Aboriginal and/or Torres Strait Islander status, priority category, diagnosis)	Service data
Effectiveness	The degree to which the intervention is producing its intended effects while assessing potential unintended consequences and changes in quality of life	Degree to which staff agree that the intended objectives of the CC are being met	Survey Interviews
Adoption	Number of settings that participate in or are exposed to the intervention. (Organisational level)	Number of sites where CC services and infrastructure have been implemented (by health facility type and region) for each CC service	Service data
	Proportion of the intended settings who deliver or are exposed to the public health intervention. (Organisational level)	Number of sites actively using CC services compared to where services and infrastructure have been implemented by not being actively used. Determined by patient volume.	Service data
	Representativeness of settings relative to the intended population who participate in or are exposed to the public health intervention. (Provider level)	Number and characteristics of front-line providers using the CC (by site, health facility type, region) for each service	Survey
	Antecedent assessment of service recipient perception (Provider level)	Front-line provider attitudes and perceptions of CC services Normalisation MeAsure Development (NoMAD) questionnaire^ 39 ^	Interviews Survey
Implementation	Consistency of delivery as intended and in the time required across staff and organisations	Fidelity: Rollout of services according to implementation plan	Service data Interviews Project initiation documents Operational guidelines
	Adaptation Assessing indicators of adaptation prior to, during, and following implementation of the intervention	Local adaptations Cultural adaptations	Survey Interviews Project initiation documents Operational guidelines

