#### Phase 2, part 1: survey

##### Survey instrument

Survey items, data collection, and analysis will be structured around the expanded RE-AIM and PRISM guidance,^
42
^ incorporating the normalisation process theory (NPT),^
43
^ and the Implementability of Healthcare Interventions.^
44
^

The survey will be divided into four parts:
1. Demographics2. Use of CC services.3. Perceptions (appropriateness, acceptability, and feasibility),^
45
^ behaviours, attitudes, and value towards using CC services.^
39
^4. Staff perception of the long-term sustainability and areas for improvement of CC services.^
40
^The survey will embed the Normalisation MeAsure Development (NoMAD) instrument,^
46
^ which covers four theoretical constructs based on NPT.^
43
^ These are coherence, cognitive participation, collective action, and reflexive monitoring and will be gathered in part 3 of the survey. NPT specifically provides greater understanding to the concepts of adoption, implementation, and maintenance (sustainment) from RE-AIM.^
47
^ Perceived risk has been shown to be a common barrier and precedent to the acceptance and adoption of technology and virtual healthcare services.^
48
^ Measures of risk to be included are based on Cunningham's^
49
^ major dimensions of perceived risk, plus additional categories appropriate to technology and service adoption.^
48
^ These categories are financial, performance, technological, psychological, social, physical, privacy, provider, and time. The three-item provider report of sustainment scale^
40
^ will be integrated into part 4 of the survey to assess sustainment.

The survey will be piloted with the research advisory team and 3 to 5 CC staff to ensure comprehension and ease of response. The survey will be anonymous and confidential to increase participation and honesty,^
41
^ consisting of a series of close-ended questions using a Likert scale, plus open-ended questions. The survey length, content, and mode of survey dissemination will be considered to maximise response.

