##### Participants, sampling, and recruitment

The survey will target the same population as phase 1, front-line providers who work in health sites across country WA. This target population is made up of nursing services and medical officers/practitioners working directly with patients, often in acute or emergency situations, totalling approximately 6000 people. The survey will target this entire population via convenience and purposive non-probability sampling; a sample size of over 362 will ensure the results will be statistically significant, with a 95% confidence level and 5% margin for error.

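### Table 2 asks the survey for the number of CC users by site, but the survey is sized for one whole-population percentage and a volunteer sample cannot count users

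*Protocol article*

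**What the plan says.** Table 2 (Proposed phases, data collection, and analyses) has a provider-level Adoption row on representativeness. Its measure is "Number and characteristics of front-line providers using the CC (by site, health facility type, region) for each service", and the survey is its only listed source. Phase 1 states that the service data hold no data on individual staff, so no other listed quantitative source can supply it.

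The survey's size is set under Participants, sampling, and recruitment in Phase 2, part 1. The target group is described as "totalling approximately 6000 people". On sampling: "The survey will target this entire population via convenience and purposive non-probability sampling". On size: "a sample size of over 362 will ensure the results will be statistically significant, with a 95% confidence level and 5% margin for error". No size or margin is given for any subgroup. The survey's Data analysis section names descriptive statistics only.

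On the number of sites, the Setting section says "There are 103 WACHS-run health facilities" and splits them into 6 large regional hospitals, 15 district hospitals, 48 small hospitals, and 34 health centres and nursing posts, in seven regions. Model of service says the CC is enabled in 87 of the 103 and names five services. On confidentiality, Survey instrument says "The survey will be anonymous and confidential to increase participation and honesty".

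**The concern.** The size statement and the Table 2 row do not fit together. One fixes a sample that suits a single overall percentage. The other asks the same sample for results at site level, for each service. The size statement also says without restriction that the results will be significant, so nothing tells the reader that the site level lies outside what the sample can support.

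There is a separate problem with the word *Number*. Counting the providers who use the CC at a site needs a census or a probability sample of that site's staff. Volunteers supply neither.

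What is at stake is how adoption is interpreted. Table 1 asks about differences in reach and adoption across regions, sites and facility types, and Phase 3 uses survey data to explain the service data. Site-level survey figures resting on a few volunteers could be taken for real differences in adoption and feed into recommendations.

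**Working it through.** **Inputs from the protocol article.** Population about 6000; minimum sample 362; 95% confidence; 5-point margin; 103 sites, 87 enabled; 7 regions; 4 facility types; 5 services. **Assumed, not stated:** p = 0.5, and responses spread evenly over sites unless noted.

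**1. Reproduce the plan's figure.** For one proportion:
- n0 = 1.96² × 0.25 / 0.05² = 384.1
- with finite population correction, n = 384.1 / (1 + 383.1/6000) = 361.1, rounded up to 362

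The stated size is reproduced exactly, as the requirement for one percentage in the whole population under random sampling.

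**2. Respondents per site at the minimum.**
- 362/103 = 3.5 per site
- 362/87 = 4.2 per enabled site

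If every respondent answers about all five services, these remain the denominators for each service. If responses were divided among services, they would fall to 362/515 = 0.7 and 362/435 = 0.8. The conclusion is the same either way.

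**3. Precision at a site.** The normal approximation is not valid at n of about 4, so the exact binomial interval is used. For 2 users among 4 respondents, the 95% interval is 7% to 93%.

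**4. More responses than the minimum.** Half-width = 1.96 × √(0.25/n) × √((N − n)/(N − 1)), with N = 6000/103 = 58.3 staff at an average site. At 1200 responses:
- n = 1200/103 = 11.65
- half-width = 1.96 × √(0.25/11.65) × √(46.6/57.25) = 0.26, or about 26 points either way (approximate at this n)

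A 10-point margin at an average site needs 96.04 / (1 + 95.04/58.3) = 36.5 respondents. Over 103 sites that is about 3760 responses, or 63% of staff.

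**5. Uneven sites.** The protocol gives no staffing by site. Small hospitals, health centres and nursing posts make up 48 + 34 = 82 of 103 sites (80%). If response follows staff numbers, a site with an assumed 10 staff has a 54% chance of no respondent at all (hypergeometric, 362 drawn from 6000). A site of 58 staff has a 73% chance of fewer than five.

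**6. Contrast with pooled levels, for illustration only.** An even split gives 362/7 = 51.7 respondents per region and 362/4 = 90.5 per facility type. With the formula in step 4 (N = 857 and 1500) the half-widths are about 13 and 10 points. They presume random sampling and equal groups. The design has no random sampling, and equal groups are implausible with 6, 15, 48 and 34 facilities. They show only that pooling is far less imprecise than reporting by site.

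**The case against.** The strongest reply has four parts.

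- **362 is a floor.** All staff are invited, with two reminders and several other recruitment routes. A reader might take 3.5 per site as the expected yield, and the protocol does not support that: 3.5 is the average at the stated minimum, and large hospitals would have more. This stands as a qualification. It does not rescue the site level, as the figures for 1200 and 3760 responses show.

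- **Table 2 lists data to be collected and claims no site-level precision.** The row concerns representativeness, the survey analysis is descriptive, and the Discussion acknowledges volunteer bias and convenience sampling. This limits the seriousness of the point. The row still fixes a by-site result from this survey, and describing a sample as descriptive does not turn it into a count of users.

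- **Site-level use already comes from the service data.** This is largely true: reach by site and active use of the CC by site both rest on patient volume. It makes the by-site survey figure less necessary. It is not a full substitute, because service data count episodes and not providers.

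- **Anonymity.** A reader might infer that the plan breaches its own promise at small sites. The documents do not show this. No section says that site-by-characteristic cells will be published. The survey's Data collection section keeps contact details apart so that responses stay non-identifiable. The interview section promises that all reporting will be aggregate or non-identifiable, and the Discussion undertakes to ensure participant confidentiality. A small-cell rule may sit in a fuller document, so its absence is no finding. What remains is a secondary risk: provider characteristics by site and service, at a handful of respondents per site, sit uneasily with those promises.

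**Conclusion.** The point holds for the site level and for the word *Number*. The survey is sized for one overall percentage. At that minimum it averages 3.5 respondents per site (4.2 per enabled site), where 2 of 4 is compatible with anything from 7% to 93%. A response more than three times the minimum would still leave about 26 points either way at an average site. These figures assume p = 0.5, an even spread and random sampling. The sampling described is non-probability, so the true uncertainty is not captured by any of these margins.

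That a volunteer sample cannot count users needs none of those assumptions and holds at any realistic response. The claim of ensured significance is also misplaced: a margin of error describes precision, and the survey analysis names no test.

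The point does not extend to region and facility-type summaries as such, nor to a demonstrated breach of anonymity. It is worth correcting because the row commits the plan to site-level counts that its design cannot deliver.

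**What to change.** - **Table 2, provider-level Adoption row sourced from the survey:** delete *by site*, or pool to region and facility type. Replace *Number* with *proportion of respondents reporting use*.
- **Participants, sampling, and recruitment (survey):** state that the 5% margin is nominal, refers to whole-sample percentages only and presumes random sampling. Delete the words saying that the size will ensure statistical significance.
- **Site-level activity:** keep it on service-data episode volume, as already planned, and note that this counts episodes and not providers.

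Do not write fixed margins for region or facility type into the plan, because they would depend on random sampling and equal groups. The documents give no basis for a particular minimum cell size either.

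The cost is a few words in two places and no extra respondents. The downside is that site-level survey tables are given up. Dropping them also reduces the secondary anonymity risk.

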### Theoretical frameworks

An Implementation Science lens will be employed in this research. The expanded RE-AIM framework will be used, which combines the practical, robust, implementation, and sustainability model (PRISM),^
34
^ and the IOF.^
35
^ RE-AIM is a planning and evaluation framework used to assess impact of an intervention at the individual and organisational level for the indicators of reach, effectiveness, adoption, implementation, and maintenance.^
36
^ PRISM was developed to assess contextual factors affecting RE-AIM. This includes the intervention characteristics; perceptions and characteristics of individuals and the organisation; implementation and sustainability infrastructure; and the external environment.^
37
^ The IOF includes eight implementation outcomes which can influence the success of an intervention: Acceptability; Adoption; Appropriateness; Costs; Feasibility; Fidelity; Penetration; and Sustainability. Reilly, Kennedy^
33
^ mapped these implementation outcomes to the RE-AIM indicators, with working definitions. The enhanced mapping of implementation outcomes to RE-AIM indicators will be used to guide data collection, analysis, and the triangulation of results. This will inform how multi-level contextual factors may influence implementation outcomes, and therefore service outcomes, including efficiency, safety, effectiveness, equity, patient-centredness, and timeliness, which are all indicators of success for the intervention.^
35
^ Analyses of these indicators will be used to inform evidence-based recommendations to improve the implementation and sustainment of this model of care in the long term.^
38
^

#### Phase 1: command centre service data analyses

Data from each of the CC services will be collated from the date of implementation, or when useful data collection commenced, to the date of data extraction. These vary based on the service, with dates to be outlined on analyses.

Variables to be collected and analysed for each service are framed around the evaluation of implementation status and implementation outcomes, integral and proceeding to successful service and clinical outcomes.^
35
^ Service data will be collected for all ‘service contacts’ across the 103 WACHS-run health facilities, which were referred to the CC. No individual staff data are collected in the service data, therefore ‘Episode’ volume will be used to demonstrate the reach (patient level) and adoption (organisational level), as outlined in Table 2.

CC service data will be analysed via descriptive statistics including measures of frequency, percentages, central tendency, and variation. The analyses will describe each CC service, by site, by region, and by health facility type. Prior to analyses, the data will be transformed into a suitable format across the services to enable cross-tabulation across variables. The data will also be checked for missing or not applicable data or the presence of any anomalies. Inferential statistics will be used to test for analysis of variance between patient contacts (dependent variable) and the region, health establishment type, and site (Independent variables), per service.^
41
^

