^ identified key knowledge gaps and specific recommendations to build evidence on the emerging use and effects of RPPT. Highlighted was the inconsistent evaluation, implementation, and sustainment of these services, recommending that conceptual frameworks be used, and contextual factors be considered. Additionally, Wakefield et al.^
20
^ calls for new research efforts to understand the value and effects these services deliver, with an aim to improve health outcomes for rural and remote patients, by supporting the local workforce and improving access to healthcare.

This research intends to strengthen the evidence base of RPPT by providing methodologically sound research to fill knowledge gaps and recommendations identified by Totten et al.^
19
^ and Wakefield et al.^
20
^ Recommendations identified by these authors^
20
^ that this research intends to cover include:
The variation of uptake across diverse settings, organisational structures, and provider types.The standardisation of measures across multiple sites to assess outcomes and impact.Evaluate whether RPPT impacts rural provider recruitment and retention.Engage providers to shape and evaluate RPPT to better meet community and population needs.Examine sociocultural factors that may influence uptake, outcomes, and sustainability.Use statistical approaches to minimise selection bias and address confounding effects.Employ mixed methodologies to triangulate qualitative and quantitative results.Specifically, this research will utilise the Western Australia Country Health Service (WACHS) Command Centre (CC) as an example of RPPT , to assess the differential implementation of RPPT across over 100 sites in country Western Australia (WA). The CC operates 24 h a day, 7 days a week, specialising in emergency, acute, and specialty clinical services, and staffed by clinical and non-clinical staff who support over 6000 front-line providers in country WA.^
23
^ The purpose of the CC is to virtually support the delivery of, and equitable access to, high-quality healthcare for people in country WA, and to complement place-based service provision.

Therefore, the overall aim of this research is to increase the understanding of provider-to-provider telehealth in rural and remote settings, including its value, benefit, and sustainment, in the WACHS.

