### Model of service

The WACHS CC began operations in 2012 as the Emergency Telehealth Service (ETS), a virtual health solution to support diagnosing, treating, and managing patients in local regions.^
26
^ The ‘Command Centre’ was officially launched in 2019 from recommendations of the Department of Health, Western Australia's Sustainable Health Review.^
27
^ A suite of services have since been implemented, beginning with the Inpatient Telehealth Service, and Mental Health Emergency Telehealth Service, and more recently, the Midwifery and Obstetrics Emergency Telehealth Service,^
28
^ and the Palliative Care Afterhours Telehealth Service.^29,30^ While these services differ in their functionality and purpose, they all deliver provider-to-provider specialist and clinical advice via virtual means, supporting the front-line clinicians caring for patients in rural and remote areas. The CC's Clinical services aims are as follows:
Facilitate appropriate decision making in the treatment and care of country patients.Support our place-based workforce by providing guidance, advice, and access to specialist knowledge to help provide the best care possible for rural and remote patients.Build a collaborative, integrated workforce, blending place-, and remote-based clinicians to deliver care to the highest possible quality and safety standard and in the most culturally appropriate way.Unlike other virtual or telehealth care, which is often between the patient and provider, these services are usually between the rural and remote front-line provider, with the patient present, and the specialist provider. The suite of CC services is enabled in 87 of the 103 health facilities.

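### The Phase 1 test on raw contact counts does not carry through Table 2's split between sites with the service and sites that have it but do not use it

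*Protocol article*

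**What the plan says.** All places are in the protocol article.

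- **Setting:** "There are 103 WACHS-run health facilities, including six large regional hospitals, 15 medium-sized district hospitals, 48 small hospitals, and 34 health centres and nursing posts".
- **Model of service:** "The suite of CC services is enabled in 87 of the 103 health facilities".
- **Phase 1: command centre service data analyses:** the data are all service contacts "across the 103 WACHS-run health facilities, which were referred to the CC". The same section says of the volume measure: "Episode’ volume will be used to demonstrate the reach (patient level) and adoption (organisational level), as outlined in Table 2". It then specifies an analysis of variance, per service, with patient contacts as the dependent variable and region, establishment type and site as the independent variables. Data for each service run from that service's start, or from when usable data began.
- **Table 2, Reach:** "Proportion of CC patient contacts compared to total health facility presentations".
- **Table 2, Adoption:** one row counts the sites where each service is installed, by type and region. The next begins "Number of sites actively using CC services compared to where services and infrastructure have been implemented" and goes on to set these against installed sites that are not in active use, judged by patient volume. Both rows give service data as their only source.
- **Discussion, third limitation:** the services went live at different times and places. The remedy offered is to analyse the same variables across services.

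**The concern.** The number of contacts at a site depends on whether the service was there, for how long, how many patients came, and how readily staff used it. Only the last is uptake. The inferential sentence in Phase 1 puts the raw count on the left-hand side and does nothing to separate the four.

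The extract adds a second difficulty. A file made of referred contacts cannot by itself show whether a site with no rows lacked the service or had it and left it unused. Depending on how the file is handled, the enabled but unused sites disappear, or the sites without the service are counted as low users.

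This bears on the research questions in Table 1. Objective 1 asks how reach and adoption differ between regions, sites and facility types, and Objective 2 asks what lies behind differential use. A facility type with few enabled or late-enabled sites would look like a type whose staff are reluctant. Lack of access and lack of uptake call for different recommendations.

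**Working it through.** **Inputs.** Facility counts of 6, 15, 48 and 34 (Setting); 87 enabled of 103 (Model of service); about 200,000 contacts across the suite since 2012 (Population, used only for scale).

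**1. The plan's own figure.** 6 + 15 + 48 + 34 = 103, which reproduces.

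**2. Sites without the suite.** 103 − 87 = 16, and 16/103 = 15.5%.

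**3. If those 16 enter as zeros.** Let T be total contacts, all arising at enabled sites (assumption). The mean per site is T/103 against T/87 among enabled sites. The ratio is 87/103 = 0.845, so the mean is 15.5% too low whatever T is. For scale, 200,000/103 = 1,942 and 200,000/87 = 2,299.

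**4. If silent sites drop out instead.** Let A of the 87 enabled sites have any contacts. The mean over sites seen in the file is T/A, and the mean over enabled sites is T/87, so use is overstated by the factor 87/A. The documents do not give A. Assumed values:
   - A = 80: 87/80 = 1.09, about 9% too high.
   - A = 60: 87/60 = 1.45, 45% too high.
   - A = 87: no error.

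The two ways of handling the file err in opposite directions.

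**5. Comparison between facility types.** The types of the 16 sites are not stated, so these are scenarios under zero-filling:
   - all 16 are health centres or nursing posts: 16/34 = 47% of that type would be zeros for lack of the service;
   - all 16 are small hospitals: 16/48 = 33%;
   - spread evenly over both groups: 16/(48 + 34) = 16/82 = 19.5%.

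**6. Time since go-live.** Two sites with the same monthly rate r, enabled for m₁ and m₂ months, give counts r·m₁ and r·m₂. Their ratio is m₁/m₂, which is pure rollout. Starting each service's data at that service's start date does not remove this, because the date is set by service and not by site.

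**7. The passages side by side.** Table 2 makes the distinction in two adoption rows and offers a presentation denominator under Reach. The test in Phase 1 uses neither. The adoption rows name only service data as their source, and Phase 1 describes its service data as referred contacts. Project initiation documents and operational guidelines, which could supply rollout information, are listed in Table 2 only under Implementation.

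**The case against.** The strongest reply is Table 2 itself. Phase 1 defers to it for reach and adoption, and it counts installed sites, sets active sites against installed but unused ones, and relates contacts to total presentations. A reader might infer that Phase 1 as a whole mixes or loses the difference between unavailable and unused. The document does not support that: the descriptive plan keeps the two apart.

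The mention of 103 facilities can also be read as the scope of the extraction, namely all referred contacts wherever they arose. Nothing says that 103 sites enter the test or that zeros are filled in. It would go too far to say that 16 sites are forced zeros, or that 103 is the wrong number throughout; it is the right denominator for availability. Nor does the text say that staff at the 16 sites had nothing to use, since the 87 refers to the suite and single services may reach other sites. These limits stand, and they make the sizes above conditional.

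One may add that the set of sites analysed is usually left to an analysis plan. That reply stands only in part. The data scope, the outcome and the factors are all stated here, and the outcome is a raw count. An analysis plan that followed this text would still carry the rollout effect.

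A reader might extend the point to the survey, supposing that staff without access will be recorded as non-users. The instrument is not shown, so that is not supported and forms no part of this point.

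**Conclusion.** The point holds for the inferential analysis in Phase 1, and only there. As stated, the test compares raw contacts between regions, types and sites without limiting them to places and periods in which the service could be used. Differences would partly reflect where and when the Command Centre was installed.

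The size is conditional. Zero-filling the 16 sites lowers the overall mean per site by 15.5%, on the assumption that none of them contributes contacts. Dropping silent sites raises it by an amount that depends on how many there are. The effect on a comparison of types cannot be fixed from the document, because neither the types of the 16 sites, nor the number enabled for each service, nor the go-live dates by site are given.

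This is a cheap improvement to a method already fixed in the text. Table 2 shows that the distinction is intended; the test should use it.

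**What to change.** In the Phase 1 section:

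1. Name a site-by-service availability list with go-live dates as a data source beside the contact extract.
2. Report availability out of 103, for each service, as Table 2 plans.
3. Run the region, type and site comparisons for each service among enabled sites and periods only. Treat periods before go-live, and sites never enabled, as not at risk, and fill true zeros for enabled periods without contacts.

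The cost is a few sentences and one merge with rollout records. The adoption and fidelity rows of Table 2 already need that information, so no new data source is required.
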